### Interim analyses {21b}

No provisional analyses will be performed. In the event of participant discontinuity, the statistical analysis will employ intention-to-treat principles to ensure a comprehensive and unbiased evaluation of the data.

### Methods for additional analyses (e.g., subgroup analyses) {20b}

A subgroup analysis will be carried out according to sex.

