### Intervention description {11a}

Participants will be divided into two main groups: group 1 (HILT) and group 2 (sham HILT). Within each group, there will be two subgroups for men and women, determined through a simple randomization process and stratification by sex, utilizing the research randomizer program [25]. his allows the researchers to analyze the outcomes of interest by group and by subgroup. This study recognizes the superior benefits of passive stretching for flexibility improvement, post-exercise recovery, and range of motion limitations, especially in CNNP patients [26–29]. Both groups will receive as a base treatment a bilateral passive stretching exercise plan of the upper trapezius muscle, levator scapulae, and scalenes in 3 series for 30 s [27, 28]. Treatments will be performed twice a week for 4 weeks with 3 assessments: before treatment (T0), at the end of treatment (T1), and 12 weeks after treatment (follow-up) (T2).

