### Sample size {14}

The sample size was determined with the G-Power program using a power of 0.80 (1-*β*), a reliability of 95%, an error of 5% (*α*), and an effect size of *d* = 0.6 (Cohen’s *d*) with reference to previous studies that determined differences in mean pain intensity between experimental and control groups after HILT treatment with effect sizes of 0.53 [30, 40]. Based on the above, the calculated sample size is 72 subjects, with at least 36 subjects per group. The study will include 84 participants (42 per group) in recognition of the crucial role of sample size in determining the power and impact of the study. An additional 15% of participants were considered for possible losses during the follow-up (bias due to abandonment). This is consistent with what the literature recommends, which suggests including at least 10% more participants, and with the PEDro scale (criterion 8), which advocates for analyzing at least 85% of the data to maintain data validity and obtain more robust statistical results and analysis [41, 42].

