## Assignment of interventions: allocation

### Sequence generation {16a}

The selected participants will be allocated into two groups, group 1 (HILT) and group 2 (sham HILT), using a simple randomization process via the website research randomizer [25]. A block randomization with a 1:1:1:1 allocation will be performed, and participants will be stratified by sex, resulting in four subgroups with equal numbers of women and men per group (*n* = 40 per group, 20 men, and 20 women). Each participant will have an equal probability of being randomly allocated to either group 1 or group 2.

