## Statistical methods

### Statistical methods for primary and secondary outcomes {20a}

The descriptive statistics for the variables RPI, MPI, PPT, CROM, and ND will be used as analysis measures: averages and standard deviation (*x*, SD), median and interquartile range (mean, IQR), depending on the distribution of the data (test of Kolmogorov–Smirnov normality). From these data, a table will be constructed with the demographic data of the participants by group. The secondary variables sex and body mass index (BMI) will be presented with frequencies and averages or medians, respectively, according to the analysis of the normality of the data. For the inferential statistical analysis of the outcome measures, the Kolmogorov–Smirnov normality test and the Bartlet test will be used to determine the distribution of the variables PPT, RPI, MPI, CROM, and ND, and the corresponding homoscedasticity of the variances obtained for these variables in the evaluations (T0, T1, and T2). According to the results, parametric or non-parametric tests will be selected: the changes in the measurement variables within and between groups will be analyzed with the two-factor ANOVA or the Kruskal–Wallis test, depending on the distribution of the data. Subsequently, a post hoc analysis will be carried out with the Tukey or Bonferroni test, depending on the statistical differences. The significance level for all statistical tests will be set at 0.05. Data will be analyzed using IBM Statistical Package for the Social Sciences (SPSS) software (version 26; SPSS Inc.; Chicago, IL) by an investigator who is blind to group assignment.

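### Sex is the randomisation stratum, but the main model names no sex term and the sex subgroup analysis names no interaction test

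*Protocol article*

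**What the plan says.** Sequence generation {16a} makes sex the only stratification factor: "participants will be stratified by sex, resulting in four subgroups with equal numbers of women and men per group", with 20 men and 20 women in each group. Intervention description {11a} gives a reason for the sex subgroups: the scheme "allows the researchers to analyze the outcomes of interest by group and by subgroup".

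Statistical methods {20a} says that changes within and between groups "will be analyzed with the two-factor ANOVA or the Kruskal–Wallis test", depending on the distribution. The two factors are not named. In that section sex appears only as a variable to be described by frequencies. The section adds: "The significance level for all statistical tests will be set at 0.05".

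Additional analyses {20b} is one sentence: "A subgroup analysis will be carried out according to sex". It gives no method, interaction test or exploratory label.

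**The concern.** Two things do not fit together.

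- **Main model.** Stratifying removes chance sex imbalance between the arms. An analysis without the stratum leaves any sex difference in the outcome inside the error term, so the design's gain in precision is not collected.
- **Subgroup analysis.** If men and women are each tested at 0.05, the natural misreading is that a significant result in one sex and not in the other shows a sex-specific effect. It does not. With about half the sample in each test, that split is common even when the effect is the same in both sexes. The question of whether the effect differs by sex is answered by the interaction, which the article does not mention.

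**Working it through.** **Inputs.** From Sample size {14}: "using a power of 0.80", "an effect size of *d* = 0.6", reference studies "after HILT treatment with effect sizes of 0.53", 36 per group calculated, 42 per group enrolled, 15% loss. From {16a}: 20 per sex-by-arm cell. From {20a}: α = 0.05, sidedness not stated. The cell size is therefore 18 (36/2), 20 (as stated) or 21 (42/2). The 40 and 42 per group need reconciling, but this barely moves the results.

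**The plan's own figure.** A two-sample t test with d = 0.6, one-sided α = 0.05 and 80% power needs 36 per arm (power 0.809), so 72 in total. This reproduces. Two-sided, it needs 45 per arm, and 36 per arm give power 0.709.

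**Omitting sex from the main comparison.** Let the sexes differ by g SD in the analysed quantity (an assumption, since the article gives no value), with equal numbers of each sex in each arm. The true standard error of the group difference is unaffected. The estimated one is inflated by about √(1 + g²/4), so the test is conservative. At 40 per group, d√(n/2) = 0.6 × √20 = 2.683 and the critical t (78 df) is 1.991.

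- Adjusted: Φ(2.683 − 1.991) = Φ(0.692) ≈ 0.755.
- Unadjusted, g = 1.0: Φ(2.683 − 1.991 × 1.118) = Φ(0.457) ≈ 0.68.

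Simulation (50,000 trials):

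| g (SD) | type I error | power at d = 0.6 |
|---|---|---|
| 0.2 | 0.050 | 0.748 |
| 0.5 | 0.043 | 0.733 |
| 0.8 | 0.035 | 0.706 |
| 1.0 | 0.028 | 0.675 |

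**Separate tests in each sex, if that is what is meant.** Let p be the two-sided t-test power within one sex. The sexes are independent, so P(exactly one significant) = 2p(1 − p), P(both) = p² and P(neither) = (1 − p)². At n = 20 per cell and d = 0.6, p = 0.456, so exactly one = 2 × 0.456 × 0.544 = 0.496, both = 0.208 and neither = 0.296.

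| common true d | p (n = 20) | exactly one (n = 20) | exactly one, n = 18 to 21 |
|---|---|---|---|
| 0 | 0.050 | 0.095 | 0.095 |
| 0.3 | 0.152 | 0.258 | 0.243–0.266 |
| 0.4 | 0.234 | 0.359 | 0.337–0.369 |
| 0.53 | 0.372 | 0.467 | 0.448–0.475 |
| 0.6 | 0.456 | 0.496 | 0.486–0.499 |
| 0.8 | 0.693 | 0.425 | 0.407–0.458 |
| 1.0 | 0.869 | 0.228 | 0.203–0.282 |

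One-sided tests at d = 0.6 give 0.478–0.496. Simulation agrees with the formula. Among simulated trials with a significant overall result at d = 0.6, exactly one sex was significant in 0.58–0.61.

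**The interaction test.** With equal effects it signals a sex difference 5% of the time. At 20 per cell its standard error is √(4/20) = 0.447 SD. Power for a 0.6 SD difference in effect is Φ(0.6/0.447 − 1.96) = Φ(−0.618) ≈ 0.27. For 80% power the difference must be about 2.802 × 0.447 = 1.25 SD.

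**The case against.** The strongest reply is that much of this is inferred. The ANOVA factors are unnamed. With four sex-by-arm cells, group and sex is a possible two-factor layout, and a four-group Kruskal–Wallis test would match it. The subgroup sentence is equally compatible with an interaction test. Model terms and subgroup methods are often left to an analysis plan, which is not shown here. The precision loss may be trivial: 0.755 to 0.748 at g = 0.2, and less still if changes are analysed and a baseline sex difference cancels.

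Part of this stands. A reader might infer that the plan commits to separate within-sex tests. It does not say so; {11a} and {20b} only point that way. A reader might also take a one-sex-only result about half the time as a general property of the trial. It is close to the maximum of the curve and needs a common effect near the design value, separate 0.05 tests, and a split result being read as sex-specific. Finally, a reader might infer that omitting the stratum invalidates the main test or produces false positives. It does the reverse.

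The reply does not remove the point. The Objectives section says that the article is meant to make the statistical analysis public, and it states a main test and a subgroup analysis. Reading the factors as group and sex leaves the three assessments, and the within-group changes, without a place in the model. The Kruskal–Wallis fallback as described has no stratum term.

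**Conclusion.** The point holds in a limited form. The stratum is not named in the stated main analysis, and the stated subgroup analysis names no interaction test.

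The cost to the main comparison is power, from under 1 percentage point (g = 0.2) to about 8 points (g = 1.0) at d = 0.6 and 40 per group. This rests on an assumed sex difference in whatever quantity is analysed. Validity is not threatened.

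The subgroup risk is conditional on separate 0.05 tests and the same true effect in both sexes. Under those conditions, a split result has a probability of about 49–50% at the design effect, falling to about 10% with no effect. It is worth correcting before the data are analysed, because the correction is cheap and the misreading is predictable.

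**What to change.** - **Main model.** Name the factors and include sex as a fixed factor, as randomised. If time is one of the factors, add sex by time as well, so that the adjustment reaches the comparison of changes.
- **Rank-based fallback.** Replace Kruskal–Wallis with a rank test stratified by sex, such as the van Elteren test, and check that the chosen software offers it.
- **Subgroup analysis.** Base any statement about sex on the group-by-sex interaction estimate with its 95% CI, show the group effect in men and in women with 95% CIs, and label the analysis exploratory.

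The cost is a few sentences and one or two model terms, but also a changed fallback test. A stratified rank test gives no interaction estimate, so that estimate would still come from the linear model. The interaction will rarely settle the question at this sample size (about 27% power for a 0.6 SD difference in effect), and the report should say so. A non-significant interaction must not be presented as proof of equal effects.

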### Methods in analysis to handle protocol non-adherence and any statistical methods to handle missing data {20c}

In cases of discontinuity, the missing data will be treated according to the principle of “intention to treat” to perform an inferential statistical analysis.

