### Criteria for discontinuing or modifying allocated interventions {11b}

There will be no changes in assignments, nor will migration of individuals between groups be allowed. If people discontinue treatment, the analysis will be by “intention to treat,” recording the reasons for leaving the study.

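### Intention to treat is named as the method for missing outcomes, but it is not one, so the promised unbiased evaluation is not secured

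*Protocol article*

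**What the plan says.** Three places in the protocol article rely on intention to treat (ITT).

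- **Item 20c**, the section for missing-data methods: "In cases of discontinuity, the missing data will be treated according to the principle of" ITT. It names no other method.
- **Item 11b**, on discontinuation: "If people discontinue treatment, the analysis will be by" ITT, with reasons for leaving recorded.
- **Item 21b**, under interim analyses: "the statistical analysis will employ intention-to-treat principles to ensure a comprehensive and unbiased evaluation of the data".

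Item 20a says that changes within and between groups over T0, T1 and T2 "will be analyzed with the two-factor ANOVA" or with Kruskal–Wallis, depending on the distribution of the data, in SPSS. The sample size section (item 14) states that "the calculated sample size is 72 subjects, with at least 36 subjects per group", raises this to 84, and explains: "An additional 15% of participants were considered for possible losses during the follow-up". It also cites a quality criterion "which advocates for analyzing at least 85% of the data to maintain data validity".

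**The concern.** ITT answers two questions: which participants belong to the analysis, and in which arm. It gives no value, model or assumption for a participant who has no score at a visit. Item 20c therefore gives a non-method as the method, and item 21b attaches a guarantee to it. This is an error in what is written, not a detail left to an unseen analysis plan, because a plan that named a real method would have to replace the sentence.

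Without a working rule, the people analysed depend on how the test is set up:

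- If the two-factor ANOVA is run as repeated measures in SPSS, anyone missing a visit is dropped, including an observed T1 score.
- Kruskal–Wallis by visit keeps whoever has a score at that visit, which is a different set. The choice between the two tests rests on a distribution check made after the data are in.
- A reader could also take ITT to mean carrying the last score forward, which gives a third answer.

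The follow-up comparison is part of the main purpose (Objectives), and follow-up runs to week 20. Loss related to pain is plausible. Item 11d bars starting other treatments or medications during the trial, and the eligibility criteria list analgesic use during the study as an exclusion. Item 17a says participants are not blinded, although Trial design says they are. If they are not, unequal loss between arms is more plausible.

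**Working it through.** **1. The plan's own figures.** Inputs from item 14: d = 0.6, power 0.80, α = 0.05. The normal approximation, one-sided, gives n = 2(1.645 + 0.842)² / 0.6² = 34.4, so 35 per group. The exact t-test gives 35.04, so 36 per group and 72 in total, as stated. The loss allowance is 36 × 1.15 = 41.4, so 42 per group and 84 in total, as stated. The figures reproduce one-sided only; that is a separate matter.

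**2. What the allowance covers.** 84 × 0.85 = 71.4 participants, or 35.7 per group. One-sided power at 35.7 per group is 0.81, the planned level. The allowance covers the loss of numbers. It does nothing about who is lost.

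**3. Bias from using observed scores only.** Let a share p of one arm be missing, and let their mean differ from that of the observed participants by k SD. The full-arm mean is observed mean + p·k, so the bias is p·k. The documents give no k, so a range is shown with p = 0.15:

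| k (assumed) | Bias (SD) | Share of d = 0.6 |
|---|---|---|
| 0.25 | 0.0375 | 6% |
| 0.5 | 0.075 | 12.5% |
| 1.0 | 0.15 | 25% |

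The direction depends on which arm loses whom. If there is no true effect and the bias favours HILT, then with 36 per group (standard error √(2/36) = 0.236 SD) a nominal one-sided 5% error becomes about 6.9%, 9.2% and 15.7%. A two-sided 5% error becomes about 5.3%, 6.2% and 9.8%.

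**4. Illustration with pain-related loss.** All inputs except the 15% and d = 0.6 are assumptions: NPRS SD 2 (so the difference is 0.6 × 2 = 1.2), correlation 0.6 between visits, and 15% lost between T1 and T2 by a logistic model on T1 pain. Differences below are among participants with all three visits (true value 1.2). Repeated simulations agree to about 0.01 point.

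| Log-odds of loss per SD of T1 pain | T1 | T2 |
|---|---|---|
| 0 | 1.20 | 1.20 |
| 0.25 | 1.19 | 1.19 |
| 0.5 | 1.16 | 1.18 |
| 1.0 | 1.09 | 1.13 |
| 2.0 | 0.95 | 1.05 |

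At the strong end, (1.2 − 0.95)/1.2 = 21% at T1 and (1.2 − 1.05)/1.2 = 13% at T2. At the weak end both are about 1%. Loss is about 18% (sham) against 12% (HILT) at log-odds 1.0, and 20% against 10% at 2.0.

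**5. If the effect fades.** Let the true T2 difference be 0.4. Under random loss, carrying the T1 score forward gives 0.85 × 0.4 + 0.15 × 1.2 = 0.52. With pain-related loss the range is about 0.51 to 0.55. Complete cases give about 0.33 at log-odds 1.0 and 0.29 at 1.5. Using all observed scores gives about 0.4. Two readings of the same sentence thus fall on opposite sides of the truth.

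**The case against.** The strongest reply has four parts.

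**Nothing in the article says complete-case.** This stands. A reader might infer that the result will be a complete-case analysis, but item 20a says two-factor ANOVA and never says repeated measures. If group and time were entered as between-subject factors, observed T1 scores would be kept. Kruskal–Wallis by visit would also use all scores available at that visit. The T1 figures above apply only to the repeated-measures form.

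**The sample size section does not contradict ITT.** This also stands. Inflating for loss is routine, and the 85% is cited as a validity threshold, not as a rule to exclude those who leave.

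**The bias is conjecture.** This stands in part. Barring other treatments does not end follow-up, medication use is recorded, discontinuers stay in the analysis (item 11b), and contact is weekly. With moderate dependence (log-odds 0.25 to 0.5) the complete-case bias is only about 1% to 4%. Log-odds of 1.0 to 2.0 mean odds ratios of 2.7 to 7.4 per SD.

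**Methods and sensitivity analyses belong in an analysis plan.** This would answer silence. It does not answer item 20c, which is not silent: it names something that cannot do the job.

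A reader might also infer a fall in power from 78% (42 per arm) to 71% (35.7 per arm). Those are two-sided figures and mix in the separate question of sidedness. On the one-sided basis that reproduces the stated size, the allowance covers the loss.

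**Conclusion.** The concern holds in a limited form. Item 20c names ITT as the treatment of missing data, ITT does not treat missing data, and the tests in item 20a do not fill the gap. The assurance of an unbiased evaluation in item 21b is therefore unsupported. The documents do not show that the analysis will be complete-case or that the result will be biased.

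The size can only be illustrated. Under the assumptions stated, complete-case differences are about 1% to 21% too small at T1 and 1% to 13% too small at T2, with no bias if loss is unrelated to pain. Carrying scores forward overstates a faded T2 effect whatever drives the loss, because that error comes from the fading. The simulated loss depends only on observed T1 pain, the condition that favours a model using all observed scores. If loss depends on unobserved pain, that model can be biased too, hence the sensitivity analysis proposed. The point should be settled before the data are analysed.

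**What to change.** Amend items 20a and 20c together, so that the new rule does not conflict with the old tests. State that:

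- all randomised participants are analysed in their allocated arm;
- all observed T0, T1 and T2 values of each outcome enter one mixed model for repeated measures, which replaces the ANOVA or Kruskal–Wallis rule for the between-group comparison;
- no participant is deleted for a missing visit and no value is carried forward;
- as a sensitivity analysis, missing values are multiply imputed and the imputed HILT values are worsened in steps on each main outcome's own scale (NPRS points for pain, kg/cm² for pressure pain threshold) until the conclusion changes.

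In item 21b, delete the claim that the evaluation will be unbiased, or qualify it with the missing-data assumption on which it depends.

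The cost is a few sentences and one more sensitivity table. The mixed model and multiple imputation can be run in the SPSS package already named. Item 14, the number of participants and the visits need no change for this point. Other explicit methods could also cure item 20c; what matters is that one is fixed in advance.

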### Plans to give access to the full protocol, participant-level data and statistical code {31c}

N/A. Not applicable to this study.

## Oversight and monitoring

### Composition of the coordinating center and trial steering committee {5d}

N/A. Not applicable to this research.

### Composition of the data monitoring committee, its role and reporting structure {21a}

The principal researcher will be responsible for recording and organizing the data obtained in this investigation that will come from the documents and electronic records: informed consent, demographic data, clinical characteristics of the participating individuals in the research, PPT values, RPI and MPI values, cervical range of motion values, and a disability score. The metadata will be descriptive and administrative, derived from data collection, and available in the digital repository of the university library.

### Adverse event reporting and harms {22}

In general, there are minimal risks because the study will be carried out under strict safety regulations, following the recommendations of the literature and biosafety for the application of laser therapy. The exclusion criteria will make it possible to eliminate any participant with complications from phototherapy. Any harm or complication related to the treatments will be reported to the Eastern Metropolitan Health Service ethics committee for Human Research (SSMO). The same applies to possible ethical issues that may arise during the research.

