### Trial design {8}

This is a 2-arm randomized placebo-controlled superiority trial (RCT) with patient and evaluator blinded to the group allocation. This study is reported in accordance with established clinical trial reporting standards: the Consolidated Standards of Trial Reporting (CONSORT). The protocol was developed following the recommendations of Standard Protocol Elements: Recommendations for Interventional Trials (SPIRIT).

The study has been approved by the Ethics Committee of the Eastern Metropolitan Health Service (SSMO), Santiago de Chile, following the Helsinki principles (approval date: October 26, 2022. N° 20200234) [23].

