### Provisions for post-trial care {30}

During the initial evaluation session, participants will be given a document outlining all the considerations that should be made during the study period. The principal researcher will provide participants with his phone number, the researchers’ email addresses, and contact information about the physical therapy department at Andrés Bello University. The evaluators will keep an electronic record (in Microsoft Excel) of the medications taken during the week. In general, the treatments are safe and do not pose risks for the participants. However, if the individual exhibits any negative effects, they will be referred to the university health center for evaluation and treatment.

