## Assignment of interventions: blinding

### Who will be blinded {17a}

Evaluators will be blinded to the randomization and intervention processes; they will be responsible only for the evaluation procedures and will not receive information about the assignment of individuals to groups. Participants and the principal researcher responsible for the treatment will not be blinded due to the nature of the interventions.

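### The one harms rule stated covers events attributed to treatment and names no blinded judge, so any count of harms by arm would be incomplete and at risk of bias

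*Protocol article*

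**What the plan says.** Adverse event reporting and harms {22} states one rule: "Any harm or complication related to the treatments will be reported to the Eastern Metropolitan Health Service ethics committee". It does not say who decides that an event is related, by what criterion, or whether that person is blind to the arm. The same section adds: "The exclusion criteria will make it possible to eliminate any participant with complications from phototherapy".

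Provisions for post-trial care {30} states the expectation that "In general, the treatments are safe and do not pose risks for the participants", and then that "if the individual exhibits any negative effects, they will be referred to the university health center for evaluation and treatment". This second statement carries no relatedness condition, but it concerns care. It does not say that the event is recorded.

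The section on the data monitoring committee {21a} itemises what the principal researcher will record: consent, demographics, clinical characteristics, pressure pain threshold, pain intensity, range of motion and disability. Adverse events are not on the list.

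On knowledge of allocation, Concealment mechanism {16b} and Implementation {16c} have the principal researcher produce the sequence and record the data, while the treating researcher (R2) opens the envelopes and delivers both HILT and sham. Who will be blinded {17a} says: "Participants and the principal researcher responsible for the treatment will not be blinded due to the nature of the interventions". For the assessors it says: "Evaluators will be blinded to the randomization and intervention processes; they will be responsible only for the evaluation procedures". Trial design {8} differs about patients, describing a trial "with patient and evaluator blinded to the group allocation".

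Criteria for discontinuing or modifying allocated interventions {11b} states "There will be no changes in assignments, nor will migration of individuals between groups be allowed", and that people who discontinue are analysed by intention to treat with their reasons for leaving recorded.

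**The concern.** A relatedness condition placed before reporting works as a filter. If the people applying it know the arm, a skin reaction or a pain flare may be attributed to the laser more readily after HILT than after sham. The reverse can also happen if the expectation of safety is taken as given. Either way the count reflects attribution as well as harm.

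The protocol itself says that evidence on HILT in this condition is limited, and it describes the treatment as having photothermal effects. Readers of the results will want to set benefit against harm. Events never logged because nobody called them related cannot be recovered afterwards, so the matter has to be settled before data collection.

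**Working it through.** The plan gives no harm rate, no relatedness rate and no planned harms comparison, so there is no stated figure to reproduce. The check is a reading of the sections against each other, followed by an illustration.

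**Step 1. Is there another route by which all events would be captured?**

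| Section | What it provides | All-cause record by arm? |
|---|---|---|
| {22} | Related harms notified to the ethics committee | No |
| {30} | Referral for care after any negative effect | Not stated |
| {21a} | Itemised data list | Adverse events not listed |
| {11b} | Reasons for leaving recorded | Only for those who leave |

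No section shown supplies an all-cause record.

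**Step 2. Who could judge relatedness?** Four kinds of people might: the treating researcher, the principal researcher, the evaluators and the participants. The first two know the arm ({16b}, {16c}). The evaluators are blinded, but their stated duty is limited to evaluation procedures ({17a}). Participants are blinded according to {8} and unblinded according to {17a}. No section assigns the task, so judgement by unblinded staff is left open, not stated.

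**Step 3. What would differential attribution do?** Let p be the true rate, equal in both arms, and let a be the share of events judged related.

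- Reported rate in an arm = p × a.
- Reported risk ratio = (p × a_HILT) / (p × a_sham) = a_HILT / a_sham. The true rate cancels.

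Inputs: 42 per arm (Sample size {14}); p = 10% and all values of a are assumptions.

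| a HILT | a sham | Reported HILT | Reported sham | Risk ratio | Expected participants of 42 |
|---|---|---|---|---|---|
| 0.8 | 0.8 | 8% | 8% | 1.00 | 3.4 v 3.4 |
| 0.8 | 0.5 | 8% | 5% | 1.60 | 3.4 v 2.1 |
| 0.9 | 0.3 | 9% | 3% | 3.00 | 3.8 v 1.3 |
| 0.8 | 0.2 | 8% | 2% | 4.00 | 3.4 v 0.8 |

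Example for the second row: 0.10 × 0.8 = 0.08 and 0.10 × 0.5 = 0.05; 0.08 / 0.05 = 1.60; 42 × 0.08 = 3.4 and 42 × 0.05 = 2.1. The true expected number is 42 × 0.10 = 4.2 in each arm. Swapping the two shares reverses the direction (0.5 / 0.8 = 0.63). At p = 5% or 20% the ratios are the same and only the counts change. The first row shows the other failure: with equal attribution the ratio is right, but one event in five is missing from both arms.

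**Step 4. The sentence on exclusion criteria.** Read as screening, it fits Eligibility criteria {10}, which lists photosensitivity, solar urticaria, porphyria and similar conditions. However, {10} also lists burns among the skin exclusions, and analgesic use during the study. If the criteria were applied after randomisation, someone with a burn, or someone taking an analgesic for a flare, could be removed. That would not fit the intention-to-treat statement in {11b}, and it would take out the very events of interest. The text does not say which reading is meant.

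**The case against.** The strongest reply is that the sentence in {22} is about notifying an ethics committee. It does not contain the word only, and it does not limit what is recorded, analysed or published. {30} acts on any negative effect without a relatedness test. The document is a condensed article, and details of adverse-event collection commonly sit in the full protocol or the case report form. No section says who judges relatedness, and equal attribution leaves the risk ratio unbiased.

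Most of this stands and limits the point. A missing collection plan alone would not be a finding in an article. What remains is that the one rule the article does state is conditional on attribution, and that the article's own itemised data list leaves adverse events out.

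A reader might infer three stronger things that the documents do not support:

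- **That harms cannot be compared between the arms without bias.** Bias in the ratio needs attribution to differ by arm, and nothing in the text establishes that it will.
- **That {22} and {11b} contradict each other.** {11b} is silent on complications. It covers people who discontinue, and the sentence quoted from it concerns movement between groups. The exclusion sentence reads naturally as screening.
- **That a confidence limit for zero events in 42 participants measures the defect.** Such a limit reflects sample size alone and would be the same after the fix.

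It is also fair to say that the fix is partial. If participants know their arm, as {17a} says, their answers to any standard question remain open to expectation.

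**Conclusion.** The point holds as a cheap improvement to data collection. As written, the article would yield at best a record of harms filtered by attribution, with no blinded judge named and with two people who know the allocation placed to apply the filter. Incompleteness follows from the rule itself. Bias between arms is a risk, of unknown size and direction. On the assumed figures the reported risk ratio runs from 1.00 with equal attribution to 4.00 with an extreme split, and falls below 1 if the split is reversed; none of these is an estimate for this trial. The conclusion assumes that no fuller collection plan exists in a document not shown. If one does, the article needs only to state it.

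**What to change.** In {22}, state that every adverse event is recorded in both arms, whatever its presumed cause, using the same standard question at each of the 8 treatment sessions (twice weekly for 4 weeks), at the existing weekly contacts and at each assessment. Add adverse events to the data list in {21a}.

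Keep relatedness as a separate field, judged where possible by an evaluator who is already blinded, and extend the duties in {17a} to allow this. Say who asks the question at the weekly contacts: {11c} gives these to an evaluator, while {18b} gives them to the principal researcher and R2, whom {16c} makes the treating researcher.

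Tabulate all events by randomised arm, with related events as a subset. Keep the ethics-committee notification as it is.

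Clarify that the sentence on exclusion criteria refers to screening before randomisation, and reconcile it with {11b} so that a participant with a complication stays in follow-up and in the analysis. Whether and when treatment stops is for the investigators.

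The cost is one question on existing contact records, one extra field, one descriptive table, and more unrelated events to log. No change to sample size or visits is needed.
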